### Sample size

The chosen sample size was based on expected differences in three somewhat related primary endpoints. We aim to detect an effect on at least one of these endpoints with a power of 80%. Therefore, for each comparison, a two-sided alpha of 0.017 was used.

Regarding sleep duration, the estimated mean±SD at 3-month measurement is 6.2±0.9 hours for the control group.^47^ We hypothesised that this value would be 10% higher for patients randomised to CR+RESST, equating to 6.8±0.9 hours at 3-month measurement. To detect this mean difference of 0.6 hours, 49 participants per group are needed. Regarding sleep quality, the expected mean PSQI score is 6.5±2.6 at 3-month follow-up for the control group, and 4.4±2.6 for the intervention group, based on research by Ghane *et al* and unpublished data from the OPTICARE-XL trial.^48^ To detect this mean difference in PSQI of 2.1 points between the control and intervention group, 68 participants are required. For the last primary outcome, perceived psychological stress, we expect a mean PSS-10 score of 15.4±8.2 is expected after CR alone, and a mean score of 11.1±8.2 for the intervention group.^19^ To detect this mean difference of 4.3 points, 156 participants are required. Thus, accounting for a minimum of 156 participants and a dropout of approximately 25%,^49 50^ we plan to include 200 participants in the study. This sample size will also allow us to take a number of covariates into account which may be associated with intervention effectiveness.

Drop-out and adherence will be continuously monitored throughout the study. If both remain lower than expected, participant inclusion may be stopped before reaching 200 participants to prevent unnecessary burdening.

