### Statistical analysis

Descriptive statistics will be used to summarise the outcomes of the primary and secondary study parameters, as well as baseline characteristics (table 2).

Primary analyses will be conducted according to the intention-to-treat principle, but per-protocol analysis will be conducted to provide further insight into the effectiveness in adherent participants, as we aim to continue collecting data from non-adherent participants.

Linear mixed effect (LME) models will be used to study between-group differences in changes in primary and secondary endpoints between T0-T3m (primary analysis) and T0-T6m (secondary, explorative analysis). LME models can handle missing data and do not require data imputation.

To investigate whether parameters of diversity (age, sex and socioeconomic status) predict differences in changes in sleep and stress parameters between the intervention and control groups, an interaction term between randomly allocated treatment and the determinant of interest will be added to the LME model. If a significant interaction emerges, exploratory subgroup analyses may be performed.

A cost-effectiveness analysis will be performed using a healthcare and societal perspective according to the latest Dutch guidelines.^51^ A short-term time horizon of 6 months (total follow-up) will be analysed, as well as a lifetime time horizon, by using mathematical modelling for extrapolation beyond the follow-up period.^52^ Costs will include healthcare utilisation, intervention costs and productivity losses, while effects will be expressed in quality-adjusted life-years.

LMEs will also be used to examine the (bi)directional relationships between sleep, stress and lifestyle/health components. Lifestyle and health components include physical behaviour, diet intake and momentary fatigue. First, cross-sectional and longitudinal associations will be assessed using weekly averages of sleep/stress parameters and other lifestyle/health components. Additionally, day-to-day temporal relationships will be studied, while measurements on a certain moment may serve as a predictor for outcomes on a later moment. In these analyses, an outcome on a certain moment (eg, physical activity) may serve as the predictor for sleep/stress at a later moment during the day or on the following night/day, or conversely, sleep/stress at a certain moment may serve as the predictor for an outcome (eg, fatigue) during a later moment.

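### The rule for stopping recruitment before 200 requires adherence to be lower than expected, but lower adherence raises the number needed under intention-to-treat

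*Protocol article*

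**What the plan says.** The rule is in the last paragraph of Sample size in the protocol article. It first names two quantities: "Drop-out and adherence will be continuously monitored throughout the study". The next sentence is the rule: "If both remain lower than expected, participant inclusion may be stopped before reaching 200 participants to prevent unnecessary burdening".

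Three other statements bear on it:

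- Statistical analysis: "Primary analyses will be conducted according to the intention-to-treat principle". The same sentence makes the per-protocol analysis supplementary and says the team intends to keep following participants who do not adhere.
- Sample size, on the target: "We aim to detect an effect on at least one of these endpoints with a power of 80" per cent, and "for each comparison, a two-sided alpha of 0.017 was used".
- Sample size, on the endpoint that sets the total: "To detect this mean difference of 4.3 points, 156 participants are required". That figure is the minimum from which the 200 is derived, with drop-out of about 25%.

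Nothing else in the article qualifies or corrects the direction of the adherence condition.

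**The concern.** Drop-out and adherence act on the required sample in opposite ways. The 200 includes an allowance for drop-out, so if fewer participants are lost, fewer need to be enrolled to reach 156 with data. Adherence works through the effect size. A participant in the intervention arm who attends few RESST sessions but returns for measurement stays in the intention-to-treat comparison and pulls the arms together. Lower adherence than planned therefore means a smaller difference and a larger requirement.

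The sentence nevertheless makes low adherence a condition for stopping early. Taken literally it also fails in the opposite case: with low drop-out and high adherence, where a smaller enrolment is easiest to defend, the condition is not met.

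What is at stake is power for perceived stress, the endpoint with the least reserve. Inclusion began in August 2024 and was expected to run for two years, so the rule governs recruitment itself.

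**Working it through.** **Inputs, all from Sample size.** Two-sided alpha 0.017 per endpoint; power 80%; 1:1 allocation.

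- PSS-10: 15.4 against 11.1, difference 4.3, SD 8.2.
- PSQI: 6.5 against 4.4, difference 2.1, SD 2.6.
- Sleep duration: difference 0.6 hours, SD 0.9.

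**Step 1. Reproduce the plan's figures.** The normal approximation is n per arm = 2 × [(2.387 + 0.842) × SD / difference]². For PSS-10 this is 2 × (3.229 × 8.2 / 4.3)² ≈ 75.8, so 76 per arm or 152 in total. The two-sample t-test version gives 78 per arm, 156 in total, exactly as stated. It also gives 98 (49 per arm) for sleep duration and 68 for PSQI, both as stated. The figures below use the t-test.

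**Step 2. The drop-out half.** Enrolment for 156 evaluable is 156 / (1 − drop-out):

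- 20% drop-out: 195
- 15% drop-out: 184
- 10% drop-out: 174

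Lower drop-out alone supports stopping before 200. This half of the rule is sound.

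**Step 3. The adherence half.** Let f be the share of the planned difference that remains under intention-to-treat. The article gives no expected adherence, so f is an assumption, shown over a range. The PSS-10 difference becomes 4.3 × f, and the number needed grows as 1/f².

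| f | PSS-10 difference | Power with 156 evaluable | Evaluable needed for 80% |
|---|---|---|---|
| 1.0 | 4.30 | 80% | 156 |
| 0.9 | 3.87 | 70% | 192 |
| 0.8 | 3.44 | 58% | 240 |

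Hand check by the normal approximation: the standard error with 78 per arm is 8.2 × √(2/78) = 1.313. At f = 0.8, 3.44 / 1.313 = 2.620, and Φ(2.620 − 2.387) = Φ(0.233) ≈ 59%, which agrees to within a point.

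**Step 4. Both halves together.** At 10% drop-out, enrolment for 80% power on PSS-10 is 192 / 0.9 = 213.3, so 214, at f = 0.9, and 240 / 0.9 = 266.7, so 267, at f = 0.8. Both exceed 200. With no drop-out at all and f = 0.9, 192 suffice, just under 200. So lower adherence always raises the requirement, but not every combination ends above 200.

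**Step 5. The other two endpoints.** Power with 156 evaluable, applying the same f to each:

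| f | PSS-10 | PSQI | Sleep duration |
|---|---|---|---|
| 1.0 | 80% | over 99% | 96% |
| 0.9 | 70% | 98% | 91% |
| 0.8 | 58% | 95% | 82% |

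Power for at least one endpoint cannot be lower than that of the best single endpoint. At f = 0.8 it is therefore at least 95%.

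**The case against.** The strongest reply is that this is a slip of wording. The stated purpose, sparing patients needless burden, makes sense only if the trial is doing better than planned, which means less drop-out and less non-adherence. That is probably what was meant. It explains the sentence but does not correct it, because a recruitment rule should state the direction it intends.

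The rule is also permissive and conjunctive: inclusion may stop, and only if drop-out is low as well. A reader might infer that low adherence alone can end recruitment. It cannot.

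Four other stronger readings are tempting, and the document supports none of them.

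- **That the trial as a whole would lose its power and probably give a false-negative result.** The stated target is an effect on at least one endpoint, and Step 5 shows PSQI and sleep duration holding up at 80% of the effect kept. The loss concerns PSS-10.
- **That the sample size ignores non-adherence.** The PSS-10 means rest on a cited source. If that estimate already reflects ordinary non-attendance, the dilution depends on adherence relative to that source, not relative to full attendance. For example, 75% observed against an assumed 80% expected would keep about 94% of the effect (75/80). This is why f is defined as a share of the planned effect and not as the attendance rate.
- **That the rule invites stopping below 156.** The preceding paragraph gives 156 as the minimum. The rule does not repeat it, but nothing sets it aside. Thresholds and an expected adherence figure may also stand in the full protocol, and their absence from an article is no fault.
- **That an unblinded team gains an outcome-driven trigger.** The monitored quantities are drop-out and adherence, and no interim look at outcomes is described.

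**Conclusion.** The adherence condition is wrong as written and conflicts with the intention-to-treat primary analysis. The direction of the error does not depend on any assumption beyond non-adherent participants benefiting less. Its size does. With 156 evaluable, PSS-10 power falls from about 80% to about 70% if 90% of the planned effect is kept and to about 58% if 80% is kept, and restoring 80% would take about 190 or 240 evaluable participants.

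These figures assume the plan's SD of 8.2, a simple comparison at three months, and dilution in proportion to f. The consequence is confined mainly to the stress endpoint. The sample size calculation itself reproduces and is not in question here.

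**What to change.** Replace the sentence with wording such as:

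> Inclusion may be stopped before 200 only if drop-out is lower than expected, so that at least 156 randomised participants are expected to have PSS-10 data at T3m; lower-than-expected adherence is not a reason to stop early.

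This uses the plan's own minimum and ties it to the endpoint that produced it. There is no need to demand 156 on every primary endpoint, since the plan's own requirements are 98 for sleep duration and 68 for PSQI.

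The cost is one sentence in an amendment. The only thing given up is the option to use adherence as a ground for stopping early. If the intended condition was lower non-adherence, the sponsor should say so in those words and keep the reference to 156.

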### Statistical analysis

Descriptive statistics will be used to summarise the outcomes of the primary and secondary study parameters, as well as baseline characteristics (table 2).

Primary analyses will be conducted according to the intention-to-treat principle, but per-protocol analysis will be conducted to provide further insight into the effectiveness in adherent participants, as we aim to continue collecting data from non-adherent participants.

Linear mixed effect (LME) models will be used to study between-group differences in changes in primary and secondary endpoints between T0-T3m (primary analysis) and T0-T6m (secondary, explorative analysis). LME models can handle missing data and do not require data imputation.

To investigate whether parameters of diversity (age, sex and socioeconomic status) predict differences in changes in sleep and stress parameters between the intervention and control groups, an interaction term between randomly allocated treatment and the determinant of interest will be added to the LME model. If a significant interaction emerges, exploratory subgroup analyses may be performed.

A cost-effectiveness analysis will be performed using a healthcare and societal perspective according to the latest Dutch guidelines.^51^ A short-term time horizon of 6 months (total follow-up) will be analysed, as well as a lifetime time horizon, by using mathematical modelling for extrapolation beyond the follow-up period.^52^ Costs will include healthcare utilisation, intervention costs and productivity losses, while effects will be expressed in quality-adjusted life-years.

LMEs will also be used to examine the (bi)directional relationships between sleep, stress and lifestyle/health components. Lifestyle and health components include physical behaviour, diet intake and momentary fatigue. First, cross-sectional and longitudinal associations will be assessed using weekly averages of sleep/stress parameters and other lifestyle/health components. Additionally, day-to-day temporal relationships will be studied, while measurements on a certain moment may serve as a predictor for outcomes on a later moment. In these analyses, an outcome on a certain moment (eg, physical activity) may serve as the predictor for sleep/stress at a later moment during the day or on the following night/day, or conversely, sleep/stress at a certain moment may serve as the predictor for an outcome (eg, fatigue) during a later moment.

The statistical analyses will not be blinded due to limited study resources. However, the data analysis plan will be discussed with a biostatistician prior to conducting the analyses, and code will be checked by an independent researcher to prevent bias. Additionally, data and code will be made available in a data repository after study termination to promote transparency.

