Facilitators and enablers of the intervention	Semi-structured interviews with patients and healthcare professionals	Post-intervention
Momentary measures		
Perceived sleep	Electronic diary: Consensus Sleep Diary (CSD)^46^	T0, T3m, T6m
Diet	Electronic diary: Intake of caffeine and alcohol, timing of the main meal (self-designed)	T0, T3m, T6m
Momentary fatigue	Electronic diary: self-designed questions	T0, T3m, T6m
Momentary stress	Electronic diary: self-designed questions	T0, T3m, T6m
Adherence		
Adherence to CR treatment	EHR	T3m
Adherence to the RESST intervention	EHR	T3m
Baseline characteristics		
Sex	Single-item question	T0
Age	EHR	T0
Cardiac diagnosis	EHR	T0
(Changes in) Medication use	EHR	T0, T3m, T6m
Drug use	Self-designed questionnaire	T0
Socioeconomic status	Neighbourhood socioeconomic status determined via postal code (EHR)	T0
Country of origin	Single item question	T0
Country of origin of parents	2-item question	T0
Employment status and presence of irregular or night shifts	2-item question	T0
Marital status	Single-item question	T0
Educational level	Single-item question	T0

CR, Cardiac rehabilitation; EHR, electronic health record; RESST, REfining Sleep and STress; T0, baseline assessment; T3m, 3-month assessment; T6m, 6-month assessment.

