Momentary outcomes are assessed using smartphone-based ecological momentary assessment (EMA) during the 7 days the accelerometer is worn, via the MovisensXS app (Movisens, Karlsruhe, Germany). The measurement of momentary fatigue consists of three questions asking for feelings of tiredness, fitness and physical exhaustion and is based on the Short Fatigue Questionnaire.^43^ Momentary stress is also assessed with three questions, including two items from the PSS-10 questionnaire and one emotion item on nervous or stressed feelings. The questions were adapted for momentary use and previously used in EMA studies investigating momentary perceived stress.^44 45^ Prompts for momentary fatigue and momentary stress are sent six times per day, between 09:00 and 21:00 hours at random configuration, with at least 1 hour between prompts. The MovisensXS software is also used to prompt caffeine intake at 12:00 hours, 17:00 hours and 21:00 hours. Furthermore, a prompt is sent for alcohol use and timing of the main meal of the previous day using a start-of-day questionnaire. Furthermore, a sleep diary (Consensus Sleep Diary) is kept via the start-of-day questionnaire.^46^

Baseline characteristics regarding personal, disease-related and demographic measures are obtained from electronic health records and self-designed questionnaires. Attendance to the CR sessions and attendance to the intervention sessions are retrieved from electronic health records. A self-designed questionnaire is administered by a nurse via telephone to assess possible (serious) adverse events and other hospital visits.

Due to the nature of the study, blinding of participants and those giving the intervention is not possible. To minimise bias, objective measures of sleep and stress are also obtained using the GENEActiv accelerometer, as well as hair cortisol and cortisone.

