### Patient and public involvement

Patient representatives and CR professionals were involved in the initial design of the study (intervention). Additionally, a focus group interview with patients was held to evaluate the outcomes regarding completeness and relevance. The participants also provided input on the feasibility and burden of the measurements and participation in the study.

Patient meetings will be held yearly to provide input and to discuss results, where we will ensure a diverse sample of patients regarding age, sex, ethnicity, socioeconomic status and cardiac diagnosis. At the end of the study, approximately 10 interviews with patients and their relatives, and healthcare professionals will be conducted to collect information on experienced needs, barriers and enablers for further improvement and implementation of the intervention. These interviews may also guide interpretation of the differences between the intention-to-treat and per-protocol analyses, as barriers will be discussed. All interviews will be recorded, transcribed verbatim and analysed using the Consolidated Framework for Implementation Research.^53^

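### The effect in adherent participants is to come from a per-protocol contrast that, if it uses RESST attendance, selects in one arm only; a complier-average effect should stand beside ITT

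*Protocol article*

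**What the plan says.** The Statistical analysis section of the protocol article fixes the main analysis: "Primary analyses will be conducted according to the intention-to-treat principle". It then adds that "per-protocol analysis will be conducted to provide further insight into the effectiveness in adherent participants", and gives as context "as we aim to continue collecting data from non-adherent participants". It names no other estimator for the effect in adherers.

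Table 2 lists two adherence variables, both taken from health records at 3 months: "Adherence to CR treatment" and "Adherence to the RESST intervention". The Secondary outcomes section confirms the source: "Attendance to the CR sessions and attendance to the intervention sessions are retrieved from electronic health records". Under Control group and Intervention group, both arms receive standard CR and only the intervention arm receives the five RESST sessions.

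Under Patient and public involvement, on the end-of-study interviews, the article says: "These interviews may also guide interpretation of the differences between the intention-to-treat and per-protocol analyses".

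**The concern.** CR attendance exists in both arms. RESST attendance exists in one. If adherence means attending RESST, the intervention arm is reduced to those who chose to come, while the controls cannot be reduced to those who would have come. The difference between the two groups then mixes the effect of RESST with whatever separates attenders from non-attenders. A set definition in an analysis plan would make the rule explicit, but would not by itself restore comparability.

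At stake is a supplementary result: the number that readers will take as the benefit for patients who follow the programme, and the gap between that number and ITT, which the interviews may help to interpret. Part of that gap could be selection. Because the statistical analyses will not be blinded, it also matters that the adherence rule is fixed in advance.

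**Working it through.** **The plan's own figure.** The article gives no number for the per-protocol analysis. The figure that sets the trial size is 156 participants for PSS-10 (difference 4.3, SD 8.2, two-sided alpha 0.017, power 80%). A two-sample t-test calculation gives 77.24, so 78 per arm and 156 in total. It also gives 68 for PSQI and 49 per arm for sleep duration. All three match. No figure in the article is wrong on this point, and 78 per arm and SD 8.2 are used below.

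**Assumed inputs.** The article gives neither the share adherent, *c*, nor the prognostic gap, *g*, between would-be adherers and non-adherers in SD units. I take *c* from 0.6 to 0.9 and *g* from 0 to 0.5.

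**Bias in raw 3-month means (adherers versus all controls).** Write μa and μn for the untreated means of would-be adherers and non-adherers. The control mean is c·μa + (1−c)·μn, so

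bias = μa − [c·μa + (1−c)·μn] = (1−c)(μa − μn), with absolute size (1−c) × g × 8.2.

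| c | g = 0 | g = 0.3 | g = 0.5 |
|---|---|---|---|
| 0.9 | 0 | 0.246 | 0.410 |
| 0.75 | 0 | 0.615 | 1.025 |
| 0.6 | 0 | 0.984 | 1.640 |

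The range is 0 to 1.64 points, and 1.64/4.3 = 38% of the planned difference. The sign is that of the gap. It favours RESST only if adherers would have had lower PSS-10 anyway.

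**Simulation (78 per arm, 4,000 trials per scenario, gap set to favour RESST, no true effect, alpha 0.017).**
- c = 0.75, g = 0.3: the per-protocol test rejects in 3.0% of trials.
- c = 0.75, g = 0.5: 5.9%.
- c = 0.6, g = 0.5: 10.8%.
- In the same three scenarios ITT rejects in 1.8 to 1.9%, and the complier-average estimate (ITT difference divided by c) averages 0.0.

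With a true adherer effect of 4.3/0.75 = 5.73, c = 0.75 and g = 0.5, per-protocol averages 6.77 and the complier-average estimate 5.75.

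**Change from baseline.** The plan models change from T0 to T3m, not raw follow-up means. A stable gap cancels in change. If attenders merely start with lower stress and regress towards the mean, the bias is (1−c)(1−ρ) × g × 8.2 *against* RESST, where ρ is the baseline-to-follow-up correlation. With c = 0.7 and ρ = 0.5 (both assumed), 0.3 × 0.5 × 0.3 × 8.2 = 0.37 and 0.3 × 0.5 × 0.5 × 8.2 = 0.62 points. If attenders start level but improve more for reasons not seen at T0, the raw-mean bias carries over in full.

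**Where the complier-average effect fails.** It assumes that those counted as non-adherent gain nothing from being offered RESST. Take c = 0.6, g = 0.3, an adherer effect of 4.3, and a 2-point gain among those below a session cut-off:
- ITT = 0.6 × 4.3 + 0.4 × 2 = 3.38.
- Complier-average = 3.38/0.6 = 5.63 (simulated 5.67).
- Per-protocol = 4.3 + 0.98 = 5.28 (simulated 5.30).

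Both overshoot 4.3, and the complier-average estimate overshoots more.

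**Precision.** The ITT standard error is 8.2 × √(2/78) = 1.31. Dividing by c gives 1.75 at c = 0.75 and 2.19 at c = 0.6, in line with the simulated values of about 1.8 and 2.2.

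**The case against.** The strongest reply is that the article never says the per-protocol set rests on RESST attendance. CR attendance is recorded in both arms and could define the set, and definitions or adjustments may sit in an analysis plan that is not shown. This stands as far as it goes: one-arm selection is an inference, not a stated rule. But a set based on CR attendance alone would not describe adherence to the intervention under test, and adding RESST attendance to it brings the asymmetry back.

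A second reply is that the analysis is supplementary and no primary conclusion depends on it. That is correct, and it limits the weight of the point.

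A third is that the complier-average effect has its own assumption, which is doubtful with five sessions, a yes/no cut-off and unblinded participants. It also needs outcomes from non-adherers, which the trial only aims to collect while expecting about 25% dropout. This stands too, and it is why the choice of exposure definition matters.

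A reader might also infer that the per-protocol estimate feeds the implementation conclusions. The article does not say so. Interviews may help to interpret the ITT versus per-protocol difference, and barriers and enablers come from the interviews themselves.

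**Conclusion.** The point holds as a modest improvement to a supplementary analysis. The per-protocol contrast is the only stated route to an effect in adherent participants, and any version that uses RESST attendance breaks the randomised comparison in one arm. Primary ITT results and the sample size are untouched.

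The size cannot be fixed from the article. On raw PSS-10 means it is 0 to 1.6 points under the assumed ranges of adherence and gap. With change from T0 it could be smaller or point the other way.

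A reader might conclude that the analysis will favour RESST by a set amount, for instance 0.7 to 1.2 points (17 to 29% of 4.3) at 70% adherence and a gap of 0.3 to 0.5 SD. The documents do not support that: both inputs are assumed, the gap is taken as above zero and in RESST's favour, and the figure ignores the modelling of change. Nor does a complier-average effect remove the bias outright. It does so only if RESST acts solely through the attendance that has been defined.

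**What to change.** Beside ITT, report a complier-average causal effect at T3m as the estimate for adherent participants, with randomised arm as instrument and adjustment for the T0 value and centre. No RESST is planned for controls, so non-adherence is one-sided and the estimate is roughly the ITT effect divided by the share exposed.

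Define exposure before the data are analysed as any RESST attendance or as the number of sessions attended, rather than a cut-off part-way through the course. This makes the assumption of no effect without attendance more plausible. The estimate then refers to anyone who attended, or to a per-session effect, and should be described that way. If the per-protocol result is kept, state its definition for each arm and label it descriptive.

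The cost is some extra analysis. Allocation, attendance and outcomes are already planned, so no new data are needed. The downsides are intervals wider by about 1/c, dependence on the exclusion restriction, and the need to follow non-adherent participants through to T3m.

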## Methods and analysis

### Design

OPTICARE-RESST is a multicentre randomised controlled trial (RCT). Patients will be recruited from three large CR centres across the Netherlands: Capri Cardiac Rehabilitation in Rotterdam and in The Hague, and Máxima Medical Centre in Veldhoven/Eindhoven. Participants are randomly allocated in a 1:1 ratio to a 6–12 week standard CR programme (control group), or a standard CR programme with an additional behavioural intervention to improve sleep and manage stress (intervention group). A total of 200 participants will be included (figure 1). All participants need to provide signed informed consent before study entry (online supplemental material). Data are collected at the start of CR (baseline), at 3 months (post-CR) and at 6 months.

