### Patient population and randomisation

To be eligible for inclusion, participants need to (1) participate in CR at one of the study centres for any cardiac diagnosis or reason as stated in the Dutch guidelines,^1^ (2) be at least 18 years of age, (3) be proficient in the Dutch language, (4) experience poor sleep (Pittsburgh Sleep Quality Index (PSQI) >5^32^) or psychological stress (Perceived Stress Scale-10 (PSS-10) >13^33 34^) and (5) be willing to provide signed informed consent before study entry. Exclusion criteria are (1) having a severe psychiatric, cognitive or physical comorbidity that would impede CR participation and (2) active treatment for sleep disorders, stress or other forms of (behavioural) therapy at the start of the study or expected to start within 6 months that could interfere with the RESST intervention. Participants who have received prior treatment targeting sleep, stress or a related complaint (eg, continuous positive airway pressure users or sleep medication), that is still ongoing and has resulted in symptom stability in the past 3 months, are eligible.

Participants who fulfil inclusion and exclusion criteria are randomised (1:1) to the control or intervention group after baseline measurements are completed. Randomisation is performed using Castor software, which generates a random allocation sequence in variable blocks of 2, 4 and 6, stratified by participating centres. First patient inclusion took place on 28 August 2024 and is expected to last for a period of 2 years.

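### The primary contrast is worded as change from baseline but the trial was sized on 3-month values; a common baseline mean or T0 covariate, with centre in the model, would gain precision at no cost

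*Protocol article*

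**What the plan says.** Statistical analysis: "Linear mixed effect (LME) models will be used to study between-group differences in changes in primary and secondary endpoints between T0-T3m (primary analysis"). The T6m comparison is secondary and exploratory. The article does not list the terms of the primary model. It does not say whether T0 enters as a covariate, as a response with one mean for both arms, or as a response with a separate mean per arm. Centre is not mentioned in that section.

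Sample size: every endpoint is planned on follow-up values. For sleep duration, "the estimated mean±SD at 3-month measurement is 6.2±0.9 hours for the control group"; for the PSQI, "the expected mean PSQI score is 6.5±2.6 at 3-month follow-up for the control group, and 4.4±2.6 for the intervention group"; for the PSS-10, 15.4 against 11.1 with SD 8.2 after rehabilitation. Further, "for each comparison, a two-sided alpha of 0.017 was used", and the power aim is "We aim to detect an effect on at least one of these endpoints with a power of 80" per cent. No SD of change and no correlation between visits is given. The same section says in general terms that covariates can be accommodated, but names none for the primary model.

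Patient population and randomisation: allocation is 1:1 after the baseline measurements, in "variable blocks of 2, 4 and 6, stratified by participating centres".

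**The concern.** A between-group difference in change from an LME is most often read as a group-by-time term, with T0 as one of the responses and each arm free to have its own baseline mean. With complete data that is the change-score comparison. It carries the noise of both visits, and the sample size calculation does not account for this. It also ignores that randomisation makes the two baseline means equal in expectation, which is information a model can use at no cost.

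What is at stake is precision on the PSS-10, the endpoint that fixed the minimum of 156 participants. The article also allows recruitment to stop short of 200, depending on drop-out and adherence. The 156 that would guide such a decision is right for a comparison of 3-month values, and for a change comparison only at one particular correlation.

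**Working it through.** **Inputs.** From Sample size: two-sided alpha 0.017, power 80%; differences and SDs of 0.6 and 0.9 h (sleep duration), 2.1 and 2.6 (PSQI), 4.3 and 8.2 (PSS-10). From Design: 1:1 allocation. Assumed, because the article does not give it: r, the T0–T3m correlation. Equal variance at both visits and complete data are also assumed.

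**1. The plan's own figures.** A two-sample t-test on 3-month values (noncentral t) gives 49 per arm for sleep duration, 34 per arm (68 in total) for the PSQI and 78 per arm (156 in total) for the PSS-10. All three match the article exactly, including "To detect this mean difference of 0.6 hours, 49 participants per group are needed". The sizing therefore uses no baseline information.

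**2. Same effect, different variance.** T0 is measured before randomisation, so the expected difference in change equals the expected difference at T3m. Only the variance factor f, relative to a single visit, differs:

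- 3-month values alone: f = 1
- change, separate baseline means: f = 2(1−r)
- common baseline mean or T0 as covariate: f = 1−r²

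The ratio of the second to the third is 2(1−r)/[(1−r)(1+r)] = 2/(1+r). This gives 1.54 at r = 0.3, 1.33 at r = 0.5 and 1.18 at r = 0.7.

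A generalised least squares check of the mixed model agrees. For the PSS-10 with 78 per arm at r = 0.5, the standard error is 1.31 with separate baseline means and 1.14 with a common one. At r = 0.7 the two are 1.02 and 0.94.

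**3. PSS-10 power with 78 per arm** (normal approximation):

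Power = Φ(4.3 / (8.2·√(f·2/78)) − 2.387)

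With f = 1 this is Φ(3.275 − 2.387) = 81.3%.

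| r (assumed) | Change, separate baseline means | Common baseline mean or T0 covariate |
|---|---|---|
| 0.3 | 64.8% | 85.2% |
| 0.4 | 72.7% | 88.2% |
| 0.5 | 81.3% | 91.8% |
| 0.6 | 89.9% | 95.6% |
| 0.7 | 96.7% | 98.6% |

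The change analysis reaches exactly 80% when √f = 3.275/(2.387 + 0.842) = 1.014. Then f = 1.029 and r = 1 − 1.029/2 = 0.49. Below that correlation, PSS-10 power drops under 80%.

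**4. The at-least-one target.** On the change scale with 78 per arm, the PSQI has 94.5% power at r = 0.2. Even at r = 0 (f = 2) it has Φ(2.1/(2.6·√(4/78)) − 2.387) = Φ(1.18), about 88%. Sleep duration has 81.7% at r = 0.2. The chance of detecting at least one effect is no smaller than the largest single chance, so under the planned effects it stays above 80% for any non-negative r.

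**5. Centre.** If centre explains 1% to 5% of the PSS-10 variance (assumed), adjusting for it raises power on 3-month values from 81.3% to between 81.7% and 83.5%.

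**The case against.** The strongest reply is that the article names a model class and a contrast, not a full model. A reader might infer that T0 and centre are left out of the primary model. The text does not support that: it excludes neither, it mentions covariates, and it refers to a data analysis plan that is not shown. The quoted sentence is also compatible with a common-baseline model, which too estimates a difference in change from T0 to T3m. This stands, so the loss is conditional on separate baseline means being fitted.

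A reader might also infer that the trial misses its stated 80% power. That does not follow. The 80% is for at least one endpoint, and step 4 shows that the PSQI alone secures it under the planned effects. For the PSS-10 taken singly, a shortfall needs r below about 0.5, which the document neither gives nor implies. Selection at entry would lower r only in part, because patients qualify on the PSQI or the PSS-10, and accelerometer sleep is not an entry criterion. Above r = 0.5, a change analysis does better than the plan.

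Nor is it a contradiction to size on follow-up values and analyse with an LME, since the expected effect is the same on both scales. Leaving out a stratification factor generally makes the standard error conservative; it does not invalidate the test.

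What remains is that the stated contrast, read in the usual way, is less efficient than an available alternative at every r below 1, and that no stated correlation connects the sizing to the analysis.

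**Conclusion.** The point holds as a free improvement to the primary model, not as an error that undermines the trial. If separate baseline means are fitted, the analysis needs between 18% (r = 0.7) and 54% (r = 0.3) more patients than a common-baseline or T0-adjusted model for the same precision. On the PSS-10 that is a gap of 20 percentage points of power at r = 0.3, about 10 at r = 0.5 and 2 at r = 0.7. The centre part is minor: roughly 0.4 to 2.2 points under the assumed share of variance. These figures rest on an assumed r, equal variances, the planned effects and 78 evaluable patients per arm. That the adjusted model is at least as efficient as either alternative does not depend on the value of r.

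**What to change.** State the primary model in one of two closely equivalent forms, for each primary endpoint:

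- a constrained longitudinal LME with T0, T3m and T6m as responses, one T0 mean common to both arms, and arm-by-visit terms at T3m and T6m; or
- an LME on T3m and T6m with the T0 value, interacting with visit, as covariate.

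In either form, name the arm difference at T3m as the primary estimate and include centre, the randomisation stratum, as a fixed effect so that the standard errors match the design. Add a sentence saying that the sizing used unadjusted 3-month values, and give the assumed T0–T3m correlation if 156 is used to judge whether recruitment may stop before 200.

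The cost is wording only. T0 values and centre are already collected, and the sample size need not change. Because the analyses will not be blinded, the choice should be fixed before outcome data by arm are examined.
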